So far, no study has examined the dose-dependent effects of propofol on outcomes in scenarios where the maximum application rate of 4 - 5mg/kg per hour or 95 - 120mg/kg per day has not been exceeded. Furthermore, examinations of the effects of prolonged propofol administration in controlled studies have been limited to a maximum of five days.^(7)^ It is currently unknown whether the critical illness phase (early or late) in which propofol is administered also affects its unwanted effects. There is also little information on the effect of cumulative propofol doses on outcomes. A recent monocentric retrospective observational study of 839 critically ill, mechanically ventilated patients found no association between substantial cumulative propofol doses (> 500mg) and 6-month mortality.^(9)^ However, it should be noted that, without adjustment for confounders, a high cumulative dose of propofol was associated with shorter survival. This association only disappeared after adjustment, which may be related to the relatively small number of patients studied (less than 1,000).

The primary purpose of this study is to investigate the relationship between the duration of propofol therapy and daily/cumulative propofol-associated energy intake and outcomes.

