### Exposure variables

–Number of days with propofol therapy preceding transition day from one clinical state to another (numeric variable), irrespective of whether a patient had propofol on transition day or not (for definition of state transitions see Figure 1)–The cumulated amount of propofol-associated energy intake (kcal/kg) (numeric variable) preceding transition day, irrespective of whether a patient had propofol on transition day or not–The amount of daily propofol-associated energy intake (kcal/kg and day) on transition day (numeric variable)–The amount of daily propofol-associated energy intake (kcal/kg and day) (categorized variable) during different phases after ICU admission. The associations of daily propofol-associated energy intake with the outcome will be cumulated for the early phase (Days 0 - 4 after ICU admission) and the late phase (Days 5 - 11 after ICU admission).

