### Statistical analysis plan

#### Descriptive analysis

Continuous variables are described by mean, SD, median, minimum, and maximum values. In addition, two-sided 95%CIs are calculated for continuous variables. Additional descriptive statistics may be calculated as needed (e.g., quartiles, coefficient of variation, etc.). In particular, the median and interquartile range (IQR) are used to describe non-normally distributed data. Frequencies and corresponding percentages per class level describe categorical variables. Patients with missing data will be excluded. However, we will examine where and how frequently missing values occur in the data overall, how often they co-occur across variables, and whether there are notable patterns of missingness across groups. We will then derive possible limitations of this study from that analysis.

For the competing risk analyses (time-to-discharge alive, time to in-hospital death), we will classify daily propofol-associated energy intake using three thresholds that define three different levels based on the amount of propofol-associated energy received. The identification of specific energy thresholds will be based on clinical practice:^(18,19)^ level I: < 1.0kcal propofol-associated energy/kg per day; level II: 1.5 - 4.5kcal propofol-associated energy/kg per day; level III: > 4.5kcal propofol-associated energy/kg per day). Suppose there is a highly uneven distribution of patient days with a given level of propofol-associated energy intake. In that case, energy thresholds may be redefined after preliminary exploratory analysis of these data, but before assessing the association with outcome.

For converting propofol-associated energy intake into mg propofol, we will assume that the use of 1% and 2% propofol in the present study was similar to that in the multinational EuroPN study on medical nutrition therapy (2% propofol: 62%, 1% propofol: 37%, unknown: 1%; unpublished observations of the EuroPN study).^(20)^ From these data, it is possible to convert propofol-associated energy intake into mg propofol. According to Appendix A, the energy levels above would roughly correspond to the following propofol dose levels: level I: < 20mg/kg per day; level II: 20 - 60mg/kg per day; level III: > 60mg/kg per day. These propofol categories, however, will only be used to interpret results. For all statistical analyses, we will use the levels defined above based on propofol-associated energy intake.

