### Overall design of the multistate models

We will use multistate models to assess the association between cumulated daily propofol-associated energy intake preceding state transition; propofol-associated energy intake on transition day, and number of days with propofol therapy preceding state transition, adjusted for the use of MV, and the subsequent risk for an inevitable state transition (Figure 1).^(21,22)^ We will analyze state transitions on a daily basis (days 0 to 11 after ICU admission), since the database contains information on propofol use and total propofol-associated energy intake on a given day. There are no data on state transitions occurring within 24 hours. Furthermore, transitions between propofol states have only been recorded up to 12 days after ICU admission. This is because propofol data recording stopped if a patient died or was discharged from the ICU, or if they had been in the ICU for more than 11 days. In line with this, for the multistate models, we will only consider outcomes (absorbing states: in-ICU death and discharge from the ICU alive) up to day 12 after ICU admission.

All analyses (multistate models and competing risks, see below) will be performed using the Piecewise Exponential Additive Mixed Model (PAMM). Like the Cox model, this model class is a multiplicative hazards model that estimates the hazard rate (or, more generally, the transition hazards) conditional on the covariates. Coefficient estimates can be interpreted in the same way as in the Cox model, e.g., using hazard ratios. We will use the PAMM rather than the Cox model because it explicitly estimates the baseline hazard and facilitates the estimation of nonlinear and time-varying effects, as well as the inclusion of time-dependent covariates (e.g., the number of previous days on MV). The general idea is to partition the observation period into short time intervals and estimate a constant hazard rate for each interval. This enables the model to capture varying hazard rates at different times after ICU admission, making it suitable for situations where the risk of state transition changes over time (e.g., after ICU admission). In the context of a multistate model, the hazard by piecewise exponential models becomes the transition hazard. Details can be found in the references.^(9,15,23-26)^

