### Overall design of the competing risk models used to analyze time to discharge alive and to in-hospital death

The primary aim will be to analyze the association between daily propofol-associated energy intake from day 1 to day 11 after ICU admission and the time to the hospital endpoint (discharge alive with in-hospital death as a competing risk).

Recording of propofol-associated energy intake was stopped if a patient died, was discharged from the ICU, or was in the ICU for more than 11 days. However, our statistical model requires information on propofol-associated energy intake on propofol days 1 to 11 after ICU admission for all surviving patients, even if patients were discharged from the ICU before day 11. Assuming no propofol-associated energy intake after ICU discharge alive, we will impute a daily propofol-associated energy intake of 0 for these patients.

To account for the fact that a short duration of propofol therapy (and propofol-associated energy intake) may not affect outcome over a more extended period, we will use a lead-time defined as twice the number of days that a patient received propofol therapy. These lead times provide a window in which propofol-associated energy intake on a given day could have affected the subsequent day of discharge alive (time to discharge alive).

To facilitate the interpretation of the associations between propofol-associated energy intake and outcome estimated by our model, we will construct five different hypothetical propofol-associated energy intake use patterns (reflecting three different levels of daily propofol-associated energy intake (low, medium, high) on propofol days 1 to 11). These levels of use will also be used to model associations between propofol-associated energy intake and outcomes. Similar to our recent publications,^(9,15)^ we will distinguish between an early (days on propofol #0 to #4) and a late (days on propofol #5 to #11) acute phase.

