We will then use these models to compare the expected outcomes of hypothetical propofol-associated energy intake patterns, controlling for confounders. We will design six different pairwise comparisons of these artificial patterns, analyzing the events of interest (separate models for early acute phase, late acute phase, or early + late acute phase: comparison of intermediate propofol-associated energy intake *versus* low propofol-associated energy intake, and high propofol-associated energy intake *versus* intermediate propofol-associated energy intake). All adjusted hazard ratios (pairwise comparisons of different hypothetical propofol-associated energy intake patterns) will be calculated assuming ceteris paribus.

The primary objective of the analysis of propofol-associated energy intake is to obtain the cumulative incidence function of the events of interest (time-to-discharge alive, taking into account the competing event of in-hospital death). We will again use PAMM. We will use techniques employed in previous publications^(9,15)^ to model cumulative effects where past values of a propofol-associated energy intake influence the hazard on a given day after ICU admission. This is relevant when accumulated propofol exposure may increase the risk of an event.

To model the cumulative effects over the follow-up period, we will use the lead time described above. This describes the time interval during which a propofol-associated energy intake registered on a given day after ICU admission affects the likelihood of hospital discharge alive or in-hospital death. We will first create the piecewise exponential data format by constructing covariate matrices for propofol-associated energy intake, additional matrices representing the time of exposure, and a lead matrix defining the time window during which the event of interest (hospital discharge alive or in-hospital death) will be recorded. Furthermore, we will divide the time axis after ICU admission into segments (Day x to Day x + 1 after ICU admission), assuming a constant exponential distribution within each segment.

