Propofol-associated energy intake is a time-dependent covariate characterized by time-varying exposure. This time-varying exposure can be described by an individual's exposure history, in which a specific value of propofol-associated energy intake is attributed to each day after ICU admission. To model the cumulative associations, we will first compute the partial association over the time window containing the aforementioned segments, in which the value of propofol-associated energy intake on a given day after ICU admission can affect the hazard rates. For cumulation, we will use the weighted cumulative exposure model,^(28)^ in which the partial associations are assumed to be linear and depend only on the time window. This model is defined as the definite integral of the partial associations over the entire time window. Furthermore, the model computes the cumulative associations between time-varying propofol-associated energy intake and recency.

For the primary analysis, we will first fit cause-specific hazard models for each event type, and then combine the resulting models to estimate the cumulative incidence function for each event type.^(15)^ The cumulative incidence function is calculated by considering the probability of hospital discharge alive or in-hospital death until the end of the lead time. For comparison, we will also use the Fine–Gray subdistribution hazard model to analyze predictors (including the cumulative association of propofol-related energy intake) of time-to-discharge alive.^(29)^

The Fine-Gray model is a type of proportional hazards model used to estimate the probability of the event of interest (hospital discharge alive) occurring, while accounting for in-hospital death (a competing risk), which can prevent a patient from being discharged alive from the hospital. The Fine-Gray model directly estimates the cumulative incidence function of the cause of interest (discharge alive), and the advantage of this model is that the effects of covariates and exposures can be interpreted directly with respect to the cumulative incidence function. The general estimation approach will be equivalent to the cause-specific approach described above; however, there will be no need to model the competing event directly.

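### The primary dose-response analysis cuts recorded kcal/kg into three levels and compares only adjacent ones; a numeric dose term and a high-versus-low contrast should be added

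*Protocol article*

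**What the plan says.** The Abstract names the dose-response relationship as the aim, and Research question names evidence on safe dosing and duration.

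- **Form of the exposure.** Exposure variables lists, for the phase-based analysis, "The amount of daily propofol-associated energy intake (kcal/kg and day) (categorized variable) during different phases after ICU admission". Table 2 ties this categorised form to the primary outcomes. Numeric kcal/kg, cumulated or on the transition day, is kept for the multistate models, whose endpoints are ICU death and ICU discharge up to about day 12.
- **The levels.** Descriptive analysis places level I below 1.0 kcal/kg per day and continues "level II: 1.5 - 4.5kcal propofol-associated energy/kg per day; level III: > 4.5kcal propofol-associated energy/kg per day". It then says "For all statistical analyses, we will use the levels defined above based on propofol-associated energy intake".
- **Use in the model.** The competing-risk section says of the three levels: "These levels of use will also be used to model associations between propofol-associated energy intake and outcomes".
- **Contrasts.** "We will design six different pairwise comparisons of these artificial patterns, analyzing the events of interest". They are intermediate versus low and high versus intermediate, each for the early phase, the late phase and both together.
- **Functional form.** In the weighted cumulative exposure model, "the partial associations are assumed to be linear and depend only on the time window". The multistate section gives as one reason for choosing the piecewise exponential additive mixed model (PAMM) that it "facilitates the estimation of nonlinear and time-varying effects".

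**The concern.** A graded association can be spread over both steps, low to intermediate and intermediate to high, without either step being large enough to exclude a hazard ratio of 1. If only the two steps are reported, no single estimate or test addresses the gradient, which is what the study sets out to describe. The open top level adds to this: an association confined to the highest intakes is averaged with intakes just above 4.5 kcal/kg.

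The linearity statement leaves the model itself unclear. If the partial association is linear in numeric kcal/kg, the exposure is not categorised, and both adjacent contrasts are multiples of one slope. If it is linear in level indicators, a coarse three-step shape is estimated and differences in dose within a level are ignored. The article supports neither reading over the other.

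**Working it through.** **The article's own figures.** Events: 18,000 × 0.70 = 12,600 discharges, consistent with more than 10,000 in Sample size considerations. Appendix A: 1 / [(1.8 × 1.1)/(2.8 × 20) + 1.1/(2.8 × 10)] = 13.4 mg/kcal, against a stated 13.5. With 13.5, 4.5 kcal/kg is 60.75 mg/kg and 1.5 kcal/kg is 20.25 mg/kg, matching the stated 60 and 20. Level I is therefore taken as below 1.5 kcal/kg here, as in Subgroup analysis; the 1.0 in Descriptive analysis would be 13.5 mg/kg.

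**Power: inputs and formulas.** The article gives no intake distribution, effect size or power. Assumed: a log-linear hazard with slope b per kcal/kg, D events, two-sided 5%. With level shares p and level means m, the information is:

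- numeric term: D × Var(x) × b²
- contrast of levels i and j: D × [p_i p_j/(p_i + p_j)] × (m_i − m_j)² × b²
- three levels jointly: D × (between-level variance) × b²

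The slope is set so that the numeric term has 80% power (noncentrality 1.96 + 0.84 = 2.80). Another test keeping a fraction f of the information has noncentrality 2.80 × √f.

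**Worked example, intake uniform on 0-8.9 kcal/kg.** Shares 0.169, 0.337, 0.494; means 0.75, 3.00, 6.70; variance 8.9²/12 = 6.60.

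- II vs I: [0.169 × 0.337/0.506] × 2.25² = 0.57; f = 0.57/6.60 = 0.09; power 13%.
- III vs II: [0.337 × 0.494/0.831] × 3.70² = 2.74; f = 2.74/6.60 = 0.42; power 44%.
- Three levels jointly: within-level variance (0.169 × 1.5² + 0.337 × 3² + 0.494 × 4.4²)/12 = 1.08; f = 1 − 1.08/6.60 = 0.84; power on 2 df 63%.

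**Range over 11 assumed distributions** (uniform 0-7.0 and 0-8.9; gamma of shape 2, mean 1.5, 2.5 or 3.5, with 0, 30 or 60% zero-intake days, limited to 8.9):

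| Test | Information kept | Power |
|---|---|---|
| Numeric, 1 df | 100% | 80% |
| II vs I | 9-61% | 13-59% |
| III vs II | 6-44% | 10-46% |
| At least one of the two, unadjusted | – | 52-65% |
| Three levels, 2 df | 74-91% | 57-67% |
| Trend over three levels, 1 df | 74-91% | 67-76% |
| III vs I (not planned) | – | 22-73% |

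The cut alone therefore loses 9-26% of the information. A single adjacent contrast loses 39-94%.

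**Which outcome.** With about 70% discharged alive, deaths cannot exceed 0.30 × 18,000 = 5,400. Censoring at day 60 and the lead-time window lower this further. As an illustration with 2,000 deaths and a hazard ratio of 1.03 per kcal/kg, four of the distributions give 26-92% power for the numeric term, 17-30% for II vs I and 5-59% for III vs II.

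**Top level.** The Introduction cites scenarios in which "the maximum application rate of 4 - 5mg/kg per hour or 95 - 120mg/kg per day has not been exceeded". Level III starts at about 60 mg/kg per day, so it pools (95 − 60)/95 = 37% to (120 − 60)/120 = 50% of that range.

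**The case against.** The strongest reply is that the analysis answers the question as posed. Research question speaks of defined levels of intake and Outcome measures of comparing two levels; numeric intake is deliberately secondary. In context, "For all statistical analyses, we will use the levels defined above based on propofol-associated energy intake" chooses kcal levels over mg levels, not categories over numbers. Both points are fair. The categorisation rests on Exposure variables, Table 2 and "These levels of use will also be used to model associations between propofol-associated energy intake and outcomes", and it still sits beside a dose-response aim with no estimate of the gradient for the hospital outcomes.

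A reader might infer that the three-level cut throws away most of the power. It does not: the cut costs 9-26% of the information, and the pair of contrasts together does better than either alone. Nor are large effects at risk for discharge. With 10,000 events and a hazard ratio of 1.05 per kcal/kg, II vs I has 96-100% power in the four distributions examined, and III vs II has 98-100% in three of them; it falls to 22% where level III holds about 1% of days. The plan allows thresholds to be redefined, before outcomes are assessed, if the distribution is very uneven.

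The 80% benchmark belongs to a 1-df linear term. A flexible smooth, treated as a fixed test on 3 to 5 df at the same noncentrality, would have about 56-64%, no better than the 2-df level test. So power does not argue for making a smooth the main test.

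A reader might also infer that the top level hides half the dose range and that finer modelling would locate harm near the maximum. Half holds only at 120 mg/kg; at 95 it is 37%, and this is a share of the dose range, not of patient-days. Concentration is unrecorded: 7.04 kcal/kg (95/13.5) is 6.4 mL/kg, which is 64 mg/kg if all 1% and 128 mg/kg if all 2%. That limits any kcal-based analysis.

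Finally, the plan states no significance rule, and a high-versus-low ratio is the product of the two adjacent ratios. Its confidence interval, however, is not planned.

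**Conclusion.** The point stands in a limited form. For discharge alive and in-hospital death, a numerically recorded dose is categorised and only adjacent levels are compared, so the primary analysis contains no direct estimate or test of the gradient it aims to describe. The linearity statement also needs to be reconciled with the categorised exposure. Relative to a 1-df numeric term at 80% power, each planned contrast has roughly 10-59%. The shortfall comes mainly from relying on adjacent contrasts and bears most on in-hospital death.

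All power figures rest on assumed intake distributions, a log-linear effect and a single scalar exposure. They ignore within-patient correlation, confounder adjustment and the weighting over the lead-time window, and they apply only if the levels really replace the numeric value in the model. This is an inexpensive improvement that serves the stated aim; it does not invalidate the planned contrasts.

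**What to change.** In the cause-specific cumulative-exposure PAMMs for discharge alive and in-hospital death:

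1. Add daily intake as a numeric kcal/kg term. Pre-specify the linear version as the 1-df dose-response test, with its estimate and 95% CI.
2. Fit a penalised smooth in dose as a secondary look at shape, with its confidence band.
3. Add a high-versus-low contrast with 95% CI for early + late. The low/low and high/high patterns are already needed for the planned early + late comparisons.
4. Keep the six three-level contrasts for presentation.
5. Reword the linearity sentence in the competing-risk section to say what the partial association is linear in (numeric kcal/kg or level indicators), consistently with Exposure variables and the statement on modelling by level. Limit the sentence in Descriptive analysis on using the levels for all analyses to the competing-risk models, since the multistate models use numeric intake.

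The cost is wording and one extra model specification on data already held. The downside is a curve that will be imprecise at sparse high intakes, which the band will show. The unrecorded concentration should be stated as a limit on any reading in mg/kg.

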### Overall design of the multistate models

We will use multistate models to assess the association between cumulated daily propofol-associated energy intake preceding state transition; propofol-associated energy intake on transition day, and number of days with propofol therapy preceding state transition, adjusted for the use of MV, and the subsequent risk for an inevitable state transition (Figure 1).^(21,22)^ We will analyze state transitions on a daily basis (days 0 to 11 after ICU admission), since the database contains information on propofol use and total propofol-associated energy intake on a given day. There are no data on state transitions occurring within 24 hours. Furthermore, transitions between propofol states have only been recorded up to 12 days after ICU admission. This is because propofol data recording stopped if a patient died or was discharged from the ICU, or if they had been in the ICU for more than 11 days. In line with this, for the multistate models, we will only consider outcomes (absorbing states: in-ICU death and discharge from the ICU alive) up to day 12 after ICU admission.

All analyses (multistate models and competing risks, see below) will be performed using the Piecewise Exponential Additive Mixed Model (PAMM). Like the Cox model, this model class is a multiplicative hazards model that estimates the hazard rate (or, more generally, the transition hazards) conditional on the covariates. Coefficient estimates can be interpreted in the same way as in the Cox model, e.g., using hazard ratios. We will use the PAMM rather than the Cox model because it explicitly estimates the baseline hazard and facilitates the estimation of nonlinear and time-varying effects, as well as the inclusion of time-dependent covariates (e.g., the number of previous days on MV). The general idea is to partition the observation period into short time intervals and estimate a constant hazard rate for each interval. This enables the model to capture varying hazard rates at different times after ICU admission, making it suitable for situations where the risk of state transition changes over time (e.g., after ICU admission). In the context of a multistate model, the hazard by piecewise exponential models becomes the transition hazard. Details can be found in the references.^(9,15,23-26)^

Hazard ratios can be used to describe the association of covariates and exposures with each transition (e.g., from alive to death in the ICU). In multistate settings, separate hazards are estimated for each possible transition. These individual transition hazards are then combined to obtain the overall transition probabilities by calculating the empirical transition matrix. While hazard ratios describe the direct effect on the instantaneous risk of a transition (relative risk), transition probabilities depend on the hazards of all possible transitions (absolute risk). Together, these two quantities provide a comprehensive interpretation of the underlying processes.

A particular focus will be on the concomitant use of MV, which is one of the main reasons for propofol use in critically ill patients and therefore the most important confounder of propofol-associated outcomes. The time-dependent confounder MV is considered as a separate state^(27)^ in the multistate model (Figure 1). This has the advantage that the transitions to the absorbing states "ICU discharge alive" and "in-ICU-death", and thus the transition probabilities to these states, can be modelled separately, depending on the current time-dependent propofol status (yes or no), but also on the subject-specific history of MV treatment and propofol administration (number of days with propofol therapy, cumulated propofol-associated energy intake). As the model is conditional on propofol status at any given time, but the frequency of MV use may vary between subjects within each propofol state, it allows the association of propofol and MV status with outcomes to be disentangled.

Results for the association between the exposure variables preceding transition (number of days with propofol therapy, cumulated propofol-associated energy intake (kcal/kg), propofol-associated energy intake (kcal/kg day) on transition day), and transition risk will be presented as adjusted hazard ratios (with 95%CIs) and adjusted transition probabilities (with 95%CIs) depending on a specific day after ICU admission (Days 1 to 11).

